### Sample size and power calculations

A total of 50 participants will be recruited into this study. We have allowed for a 10% drop out over the 8-week period to ensure that 45 participants will complete the study. Where appropriate, sample sizes for the primary and secondary outcome measures have been determined using weighted effect sizes calculated from randomised controlled trials of exercise training in pulmonary hypertension [15].

For the primary outcome measure, i.e. change in the 6MWT distance, the study is powered at 0.91 using a 2-tailed test for independent samples and a weighted effect size of 1.01. For the peak exercise capacity ($$ \dot{\mathrm{V}}{\mathrm{O}}_{2\mathrm{peak}} $$), this study is powered at 0.95 using an pooled, weighted effect size of 1.10 [15]. The primary measure for QoL in the current study will be the CAMPHOR. For the role physical domain in the CAMPHOR, the study is powered at 0.90 based on a weighted effect size of 0.99 [15].

The principle measure for changes in cardiac function will be made using CMRI. Recently Addetia and colleagues suggested that a per group sample size of 23 participants would detect a 5% change in right ventricular ejection fraction [34] measured using CMRI with a power of 80% and the probability of a Type I error of 0.05. The authors suggest that for a 10% change in right ventricular ejection fraction, a smaller sample size of 6 participants would be required. Based on a conservative estimate of a 5% change in right ventricular ejection fraction, the current study would have approximately 80% power to detect changes in right ventricular systolic function.

To determine the power of the current study to detect a change in clinical worsening, we have used data from previous non-RCT examining impact of exercise training on clinical worsening in PH [31] which reported the probability of being free from clinical worsening following an exercise intervention was 0.74. From REVEAL (Registry to Evaluate Early and Long-term Pulmonary Artery Hypertension Disease Management), the 2-year probability for a participant to be free from clinical worsening was 0.36 [35]. Combining these would give a risk ratio (RR) for clinical worsening following exercise training of 0.41 (i.e. = risk in exercise group 0.26/risk in control group 0.64). Based on this risk ratio, then a sample size of 45 would detect this RR with 30% power and α = 0.05 (two-tailed test). We have assumed a 5% loss to follow-up over a 2-year period. Whilst this appears conservative, individuals with PH have regular (every 3–6 months) clinic appointments to monitor progress and therapy. Although this study is underpowered to detect these long-term outcome measures, one may argue that including this outcome measure will provide important long-term pilot data for future studies.

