### Participants

Participants will be recruited over a 3 year period from the cohort of PH patients under the care of the Queensland Centre for Pulmonary Transplantation and Vascular Disease Unit at The Prince Charles Hospital, Brisbane, Queensland. Strategies for improving participant recruitment will include regular meetings with the PH clinical team and liaising with the primary PH physician (JF) and the PH assessment physiotherapist. Inclusion criteria include: age over 18 years, a confirmed diagnosis of PH based on the results of a right heart catheterization procedure (mean pulmonary artery pressure > 25 mmHg and pulmonary capillary wedge pressure < 15 mmHg) and New York Heart Association functional classification II-III. Eligible participants also will be on stable PH medical therapies and have had no exacerbations in the previous 3 months.

Participants will be excluded if they have had a change in their PH medication regime in the last 3 months or have significant co-morbidities including left-sided heart failure. Other exclusion criteria include pregnancy, recent history of light-headedness during exercise or syncope episodes in the last month and significant musculoskeletal and neurological conditions likely to adversely impact exercise performance. Patients will also be excluded if they have any of the contraindications to exercise as per the American College of Sports Medicine (ACSM) guidelines [20].

Eligible participants will be contacted by a member of the research team and provided with verbal and written information regarding the study. Informed written consent will be obtained prior to participation in the study. The study has been approved by the Metro North Hospital and Health Service - The Prince Charles Hospital Human Research Ethics Committee (HREC). Changes to the protocol will be approved by the HREC. The trial is registered with the Australia and New Zealand Clinical Trials Registry: ACTRN12616001467426.

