Long term outcomes will be analysed by examining survival and time to clinical worsening during routine follow-up clinic visits for a 2-year period following the participant’s commencement of the study. We will base this measure on the recent PH intervention studies [30–32]. For the purpose of this study clinical worsening will be defined as [30]:PH-related death orlisting for/completed lung transplantation orhospitalization for PH or clinical worsening leading to initiation of new PH-specific treatment orWorld Health Organisation (WHO) functional classification deterioration and a > 15% decrease in 6MWT from baseline.

Participants will be assessed for clinical worsening every 3–6 months following randomisation during routine clinical visits. A panel of two clinical experts, blinded to group allocation, will independently evaluate each participant for clinical worsening. Decisions will be moderated by a third expert, blinded to group allocation, in the event that the panel members reach a different decision.

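### The risk ratio of 0.41 for 2-year clinical worsening is an unadjusted cross-study ratio, not a shown training effect, and the 30% power attached to it does not follow from its own inputs

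*Protocol article*

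**What the plan says.** The power statement for clinical worsening is in the protocol article under Sample size and power calculations.

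- **Exercise risk.** The authors write that "we have used data from previous non-RCT examining impact of exercise training on clinical worsening in PH", and that this study "reported the probability of being free from clinical worsening following an exercise intervention was 0.74". That is a risk of 0.26. No follow-up time is printed with it.
- **Control risk.** From the REVEAL registry, whose printed name refers to pulmonary artery hypertension, "the 2-year probability for a participant to be free from clinical worsening was 0.36". That is a risk of 0.64.
- **Effect and power.** The two risks are divided: "Combining these would give a risk ratio (RR) for clinical worsening following exercise training of 0.41". A sample of 45 is then said to detect this ratio with 30% power at a two-sided alpha of 0.05. The section adds that the study is underpowered for long-term outcomes and that they will serve as pilot data.

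The "Participants" section describes whom the trial enrols: right-heart-catheter-confirmed PH in NYHA class II-III. It adds: "Eligible participants also will be on stable PH medical therapies and have had no exacerbations in the previous 3 months". Recent medication changes, recent syncope and significant co-morbidity are exclusions. The "Control group" section defines the comparator as usual care over the 8-week study period.

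**The concern.** The trial randomises stable patients to training or usual care. The ratio used for this outcome does not come from such a contrast. Its numerator and denominator come from two different sources, and no matching, adjustment or common comparator is mentioned. Any difference between the sources in who was studied, how long they were followed or how they were treated enters the ratio together with any effect of training. Calling the result the risk ratio following exercise training gives it a causal meaning that its construction does not support.

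Two things are at stake. A reader may take 0.41 as an evidence-based estimate of what training does to clinical worsening, an outcome that is part of the stated hypothesis. And the one power figure given rests wholly on that ratio, so it says little about what 45 participants can detect, even before asking whether the figure was computed correctly.

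**Working it through.** **Inputs.** Exercise risk 1 − 0.74 = 0.26; control risk 1 − 0.36 = 0.64; 45 participants; two-sided alpha 0.05 (all from the sample size section). Allocation is 1:1 ("Randomisation" section), taken as 22 exercise and 23 control. The planned comparison is a stratified log-rank test ("Data analysis" section); the log-rank approximation below ignores stratification.

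**The ratio.** 0.26 / 0.64 = 0.406. The printed 0.41 is correct arithmetic.

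**The printed power: two proportions.** Power = Φ[(p_c − p_e − 1.96·s0) / s1], where s0 is the pooled standard error under no difference and s1 the unpooled one.

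- Pooled risk = (22 × 0.26 + 23 × 0.64) / 45 = 0.454
- s0 = √[0.454 × 0.546 × (1/22 + 1/23)] = 0.1485
- s1 = √[0.26 × 0.74/22 + 0.64 × 0.36/23] = 0.1370
- Power = Φ[(0.38 − 1.96 × 0.1485) / 0.1370] = Φ(0.65) = **74%**

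**The printed power: log-rank (Schoenfeld).** Power = Φ[(√events / 2) × |ln HR| − 1.96].

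- HR under proportional hazards = ln 0.74 / ln 0.36 = 0.295
- Expected events = 22.5 × (0.26 + 0.64) = 20.25
- Power = Φ[(4.5 / 2) × 1.222 − 1.96] = Φ(0.79) = **78%**

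**Can 30% be reached another way?** Fisher's exact test gives 69%, a Wald test on the log risk ratio 64%, and a continuity-corrected test about 62% to 64%. Using 0.41 itself as the hazard ratio gives 53% (Schoenfeld) or 48% (Freedman). Taking a further 5% off the 45 for loss to follow-up lowers the last of these to 46%, the lowest value found. None of these reaches 30% from the stated risks. About 30% does appear if the ratio is held at 0.41 and the control risk is set near 0.30, but the printed control risk is 0.64.

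**Sensitivity to the control risk.** Exercise risk held at 0.26, same sample and alpha:

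| Control risk | Risk ratio | Two-proportion power | Log-rank power |
|---|---|---|---|
| 0.64 (printed) | 0.41 | 74% | 78% |
| 0.60 (assumed) | 0.43 | 64% | 69% |
| 0.50 (assumed) | 0.52 | 38% | 41% |
| 0.40 (assumed) | 0.65 | 16% | 17% |

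The document gives no worsening rate for stable NYHA II-III patients on usual care, so every control risk below 0.64 is an assumption made to show the range. The table shows that the choice of control source, which is the input least tied to this trial, moves the power from about 16% to 74%.

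**The case against.** The strongest reply is that the article is open about most of this. It says the exercise source was not randomised, names the registry, prints both risks and the division, declares the study underpowered for this outcome and calls it pilot data. Its background says effects on long-term outcomes are unknown, so it identifies no randomised estimate that could have been used instead. The outcome is secondary, and the sample of 50 is not derived from it. All of this stands, and it limits the weight of the point. It does not remove it: declaring low power says the trial is small for a true ratio of 0.41, not that 0.41 may not be a training effect.

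Several stronger readings are tempting, and the document does not support them.

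- **That the registry patients were at higher risk than this trial's controls will be.** This is plausible given the stability criteria, but the registry's case mix is not described beyond its name. The supportable statement is that 0.64 is not shown to apply.
- **That the printed power is overstated.** With exercise risk 0.26, 30% is too low for any control risk above about 0.47 and too high only below that.
- **That the exercise study was uncontrolled.** The text says only that it was not an RCT, and such a study can have a control group.
- **That its endpoint differs from the trial's.** The "Secondary outcome measures" section bases the measure on references 30 to 32, which include reference 31, the exercise source.
- **That 0.41 would mislead later studies through the pilot data.** Those data would be this trial's observed results, not the planning ratio.

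**Conclusion.** The point holds as a minor correction with two parts. First, 0.41 is an unadjusted ratio of a risk without a printed horizon from a non-randomised study to a 2-year registry risk, and it should not be presented as the risk ratio for training. This rests only on what the sample size section prints. Second, the 30% does not follow from 0.26 against 0.64 with 45 participants: standard methods give about 74% to 78%, and the lowest variant tried gives 46%. Correcting that number alone would not be enough, because a figure near 74% would rest on the same cross-study contrast and make the outcome look better powered than anyone can show. Nothing here affects the primary outcome, the sample size or the conduct of the trial.

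**What to change.** In the Sample size and power calculations section:

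1. Describe 0.41 as an unadjusted ratio of the risk in a non-randomised exercise study to the risk in a registry, and drop the wording that presents it as the effect of training.
2. State the follow-up time to which the 0.74 applies.
3. Replace the single 30% with power over a stated range of assumed control risks, naming the test used. For example, with exercise risk 0.26 and 45 participants, control risks of 0.40, 0.50, 0.60 and 0.64 give about 16%, 38%, 64% and 74% by a two-proportion test. Mark the values below 0.64 as assumptions.

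The cost is a few sentences. Enrolment, procedures and analysis are unchanged. The power statement becomes a wide range instead of one number, which is a fair account of what is known for this outcome.

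### The 30% power stated for 2-year clinical worsening does not follow from the protocol's own risks and sample size, which give about 69–78%

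*Protocol article*

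**What the plan says.** All the inputs are in the protocol article under Sample size and power calculations. For the exercise arm, an earlier non-randomised study "reported the probability of being free from clinical worsening following an exercise intervention was 0.74"; no time horizon is given. For the control arm, a registry is cited in which "the 2-year probability for a participant to be free from clinical worsening was 0.36". The article turns these into a risk ratio of 0.41, written as "risk in exercise group 0.26/risk in control group 0.64". It then states that "a sample size of 45 would detect this RR with 30% power", with alpha 0.05 two-sided, and adds: "We have assumed a 5% loss to follow-up over a 2-year period". The closing sentence of the paragraph begins "Although this study is underpowered to detect these long-term outcome measures" and keeps the outcome as a source of pilot data for later studies.

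Elsewhere, the 45 is what remains of 50 recruited: "We have allowed for a 10% drop out over the 8-week period". The Randomisation section sets 1:1 allocation. The Data analysis section plans Kaplan-Meier estimates and a stratified log-rank test.

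**The concern.** Risks of 0.26 and 0.64 differ by 38 percentage points. With 22 or 23 patients per arm, a gap that large should be detected far more often than three times in ten. So either the power was miscalculated or the printed risks are not the ones used, and the article does not let a reader tell which.

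What is at stake is interpretation. Delayed clinical worsening is part of the hypothesis at the end of the Background, and long-term prognosis is among the aims in the Discussion. A reader told 30% expects a non-significant log-rank result about 7 times in 10 even if the assumed effect is real. On the printed inputs that would happen about 1 time in 4 (1 − 0.74 = 0.26).

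**Working it through.** **Inputs.** Exercise risk p₁ = 1 − 0.74 = 0.26; control risk p₂ = 1 − 0.36 = 0.64; N = 45, split 23/22; two-sided alpha 0.05 (z = 1.96).

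**The risk ratio reproduces.** 0.26/0.64 = 0.406, printed as 0.41.

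**The other powers reproduce.** A two-sample t-test with 23/22 patients gives 0.91, 0.95 and 0.90 for effect sizes 1.01, 1.10 and 0.99. These match the stated powers for 6-minute walk distance, peak oxygen uptake and CAMPHOR. N, allocation and alpha are therefore being read as the article intends.

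**Two proportions, pooled z-test.**
- Mean risk = (23 × 0.26 + 22 × 0.64)/45 = 20.06/45 = 0.446.
- Null standard error = √[0.446 × 0.554 × (1/23 + 1/22)] = 0.148.
- Alternative standard error = √[0.26 × 0.74/23 + 0.64 × 0.36/22] = 0.137.
- Power = Φ[(0.38 − 1.96 × 0.1482)/0.1373] = Φ(0.65) = **0.74**.

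**Log-rank (the planned test, ignoring its stratification), taking 0.74 as a 2-year figure.**
- Under proportional hazards, HR = ln 0.74/ln 0.36 = 0.295.
- Expected events = 45 × (0.26 + 0.64)/2 = 20.25.
- Schoenfeld: Φ[½√20.25 × |ln 0.295| − 1.96] = Φ(0.79) = **0.78**.
- Freedman: Φ[√20.25 × (1 − 0.295)/(1 + 0.295) − 1.96] = Φ(0.49) = **0.69**.
- A simulated log-rank test with exponential times and 2-year censoring gives about 0.75.

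**Summary by method.** The 43 applies the 5% loss: 45 × 0.95 = 42.75.

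| Method | N = 45 | N ≈ 43 |
|---|---|---|
| Pooled z-test | 0.74 | 0.72 |
| Continuity-corrected | 0.63 | 0.60 |
| Fisher exact | 0.69–0.70 | 0.66–0.67 |
| Log-rank, Freedman | 0.69 | 0.67 |
| Log-rank, Schoenfeld | 0.78 | 0.77 |

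Two other variants at N = 45 change little: an unpooled z-test gives 0.79 and a Wald test on the log risk ratio 0.63–0.65.

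**Attempts to reach 30%.**
- Using the risk ratio 0.41 as if it were a hazard ratio, with about 20 events, still gives 0.47–0.52.
- With risks 0.26 and 0.64, the pooled test reaches 30% at about 8 per arm.
- Freedman's formula with HR 0.41 and the exercise risk applied to all patients (45 × 0.26 = 11.7 events) gives 0.30, but that contradicts the printed control risk of 0.64.
- Holding the risk ratio at 0.41 and N at 45, and lowering the control risk (an assumption; the article gives only 0.64), the pooled test gives 0.55 at 0.50, 0.42 at 0.40, 0.36 at 0.35 and 0.30 at 0.30. Fisher's test gives 0.29–0.34 at 0.35. So 30% fits a control risk of about 0.30–0.35.

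**The case against.** The strongest reply is that nothing in the design depends on this figure. The 50 patients are presented with power for walk distance, peak oxygen uptake, CAMPHOR and right ventricular ejection fraction. Clinical worsening is a secondary outcome at any power, its analysis would not change, and the error is on the pessimistic side. All of that stands, and it limits the weight of the point. It does not make 30% the right figure.

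Three stronger readings are tempting, and the article does not support them.

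- A reader might infer that the outcome was downgraded to pilot status because of a wrong number. It was secondary in any case, it remains in the hypothesis and aims, and the caveat refers to long-term outcomes in the plural. Those include survival, for which no power is given. The caveat also survives correction in a mild form, because nearly every recomputed value is below 80%.
- A reader might infer that the retention figures contradict each other, with 10% lost by 8 weeks and only 5% by 2 years. Both can hold. The first concerns completing the 8-week study and the second concerns routine clinic follow-up. Under the intention-to-treat analysis, a patient who leaves the programme can still be followed in clinic. The remark that 5% looks conservative is a matter of wording.
- A reader might infer that the 30% conceals a fragile comparison across studies. The article says openly that one risk comes from a registry and the other from a non-randomised study.

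It is also fair to object to printing a single confident replacement. The hazard ratio of 0.295 requires the 0.74 to be a 2-year probability, which the article does not say, and the source is not available here.

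**Conclusion.** The stated power is wrong as written. On the article's own inputs it is about 69–78% by the usual two-proportion and log-rank methods and 63% with a continuity correction. It is about 60–77% if the 5% loss is taken from the 45. The 30% is about half the lowest of these values and less than half of most.

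The log-rank figures assume a 2-year horizon for the 0.74, proportional hazards and no effect of stratification. The two-proportion figures need only the two printed risks, treated as 2-year risks as the article's own ratio does.

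This should be fixed, but it is not critical: it is one misstated figure for a secondary outcome, in the direction of too little power, with no effect on the sample size. Whether the calculation or the printed risks are at fault cannot be settled from the article.

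**What to change.** Recompute the power for the planned log-rank test and state four things beside it: the method, the expected number of events, whether 45 is before or after the 5% loss, and the time horizon assumed for the 0.74. If that horizon is 2 years, the entry would read: hazard ratio about 0.295, about 19–20 events, power about 67–78%.

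If 30% came from other inputs, for example a control risk of about 0.30–0.35 at a risk ratio of 0.41, correct the printed risks instead.

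In either case, reword the underpowered sentence to match the corrected figure and to rest on the uncertainty of a control risk borrowed from a different study. The cost is one paragraph, with no change to patients, procedures or sample size.

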### Data monitoring

A data safety monitoring board (DSMB) will be established to monitor the project. The DSMB will meet during the trial with the role to: monitor and review participant safety in the trial; monitor efficacy based on pre-planned interim data analyses (if required); and to review participant recruitment, accrual, retention, and withdrawal. The responsibility of the DSMB will be exercised by providing recommendations about continuing, modifying or stopping the trial. The DSMB will be advisory to the PI. A copy of the DSMB charter can be found in a secure file located on the hospital server along with all documents related to the ethical conduct of the project including the study protocol, informed consent and relevant questionnaires.

## Discussion

Despite advances in medical therapies, PH is associated with considerable morbidity and premature mortality. Patients with PH frequently report exertional dyspnoea and fatigue, functional limitation and impaired QoL. Exercise training is recognised as a valuable adjunct in the management of many chronic respiratory and cardiac conditions, with well-established benefits including improvements in exercise capacity and QoL [36, 37]. Whist a limited number of randomised, controlled exercise training studies have demonstrated similar benefits in stable PH patients, our understanding is limited with regard to the efficacy of a standard, outpatient-based exercise programs for PH, mechanisms of improvements, the potential effects on prognosis and the optimal exercise prescription parameters [38]. This has resulted in uncertainty amongst guideline developers and health care professionals in terms of recommending and prescribing exercise for this high risk patient population.

This study will be the largest randomised controlled trial to comprehensively examine the safety and efficacy of exercise training in an outpatient setting for medically stable PH patients and changes in cardiac function at rest and during exercise measured using CMRI during exercise. The specific aims of this study are to evaluate whether supervised exercise training leads to improvements in exercise capacity, cardiac function, QoL and long-term prognosis, without causing any significant training-related adverse effects. Hence, it will be the first study of its kind to evaluate the impact of exercise training on cardiac function and disease progression in the PH patient population. With the use of gold standard approaches, we will be able to determine the effect of exercise training on cardiac function during both rest and exercise, as well as whether changes in cardiac function accompany any changes in exercise capacity. As such, the results of this study will have important implications for clinical practice and future guideline recommendations.

